## Abstract

**Background:**

The wide scale and severity of consequences of tobacco use, benefits derived from cessation, low rates of intervention by healthcare professionals, and new opportunities stemming from novel communications technologies are the main factors motivating this project. Thus, the purpose of this study is to assess the effectiveness of an intervention that helps people cease smoking and increase their nicotine abstinence rates in the long term via a chat-bot, compared to usual practice, utilizing a chemical validation at 6 months.

**Methods:**

Design: Randomized, controlled, multicentric, pragmatic clinical trial, with a 6-month follow-up. Setting: Healthcare centers in the public healthcare system of the Community of Madrid (Madrid Regional Health Service). Participants: Smokers > 18 years of age who attend a healthcare center and accept help to quit smoking in the following month. *N* = 460 smokers (230 per arm) who will be recruited prior to randomization. Intervention group: use of a chat-bot with evidence-based contents to help quit smoking. Control group: Usual treatment (according to the protocol for tobacco cessation by the Madrid Regional Health Service Main variable: Continuous nicotine withdrawal with chemical validation (carbon monoxide in exhaled air). Intention-to-treat analysis. Difference between groups in continuous abstinence rates at 6 months with their corresponding 95% confidence interval. A logistic regression model will be built to adjust for confounding factors. Results: First expected results in January 2020.

**Discussion:**

Providing science-based evidence on the effectiveness of clinical interventions via information technologies, without the physical presence of a professional, is essential. In addition to being more efficient, the characteristics of these interventions can improve effectiveness, accessibility, and adherence to treatment. From an ethics perspective, this new type of intervention must be backed by scientific evidence to circumvent pressures from the market or particular interests, improve patient safety, and follow the standards of correct practices for clinical interventions.

**Trial registration:**

ClinicalTrials.gov, reference number NCT 03445507.

## Background

Tobacco use is the main cause of preventable morbidity and mortality in the world, directly accounting for five million deaths yearly [1]. The number of smokers who attempt quitting on their own every year is high, but only 2–3% remain abstinent after 12 months [2]. Healthcare professionals are very effective and efficient in their interventions on the smoker, with over threefold success rates of long-term abstinence. Combining behavioral and pharmacological treatment yields the best results [2–4].

However, only 1 in 20 attempt to quit is supervised by a professional [2]. In the public healthcare system of the Community of Madrid (Madrid Regional Health Service), 84% of smokers who attended an outpatient consultation in 2008 did not receive advice for tobacco cessation [5], a figure similar to those observed in other countries [6, 7]. Factors related to these low intervention rates have been identified, and these include lack of training for healthcare professionals and their perception that such interventions are not useful and they lack the time to implement them [8].

A possible solution is developing effective, brief, and simpler interventions, such as the “Very Brief Advice “that consists of offering the patient help to quit smoking regardless of their motivation. Many patients respond positively to this proposal, even those who had not considered making an attempt previously to the offer [9]. Compared to the usual intervention, this results in over 50% more attempts to cease smoking [10]. However, to achieve this, a resource backed by scientific evidence and easy to access must be available, such as the tobacco cessation consultations in the British National Health System (NHS).

The boom in information and communication technologies, like the internet or smartphones, open up new therapeutic perspectives. In 2016, there were 7 billion customers of mobile phone services, almost 97% of the population worldwide. Mobile broadband has continuously grown, with 84% of the world population using it [11], and the smartphone has become the main and most accessible personal computer in the majority of countries. On the other hand, patients aspire to play a greater role in their health management and increasingly search for more information in the internet (Table 1). The resulting opportunities create a new framework to empower the patient and improve clinical outcomes and health expenditure [12].

**Table 1 Tab1:** Characteristics of the web search for health information

Advantages	Downsides
Ubiquity	Unequal quality of information
Immediacy	An identified source cannot always be found
Ability to access specific population segments	The date when the content was updated cannot always be found
Automation of messages	Need to adapt the message to the targeted population
Possibility of contact and learning among peers	Risk of information overload for the patient

Translation from: Casado, S. El Papel de la Información en el empoderamiento del paciente en Basagoiti I. Alfabetización en salud. De la información a la acción [pdf]. Valencia: ITACA/TSB; 2012. ISBN: 978–84- 695-5267-4 Available at http://www.salupedia.org/alfabetizacion/

In terms of scientific evidence, a systematic review of 59 clinical trials on interventions to quit smoking via smartphones [13] concluded that text messages double the success rates of nicotine abstinence with biochemical validation, showing a risk ratio (RR) of 2.16 (Confidence interval -CI- 95%: 1.77–2.62). The relevant Cochrane review [14] comprised 12 clinical trials that included 11,885 patients, with a combined RR = 1.7 (CI 95%: 1.46–1.90) for abstinence at 6 months, and a RR = 1.83 (CI 95%: 1.54–2.19) using the data of the six clinical trials that chemically validated the abstinence, both compared to usual practice. The evaluated trials were based on interventions mainly using Short Message Service (SMS), although one employed videos, and all were conducted in high-income countries with strong policies for tobacco control. They also did not find clinical trials, published or in-progress, studying the effectiveness of applications (app) for mobile phones or tablets, despite their proliferation.

In a 2013 review about the adequacy of scientific evidence for existing apps to aid people cease smoking in the USA at the time, Abroms et al. [15] could not find any that followed science-based recommendations by clinical practice guidelines and warned about the potential negative effects on the population’s health.

In 2017, a new review [16] aimed to assess the scientific content of the most used commercial apps in the USA for helping to quit smoking as well as the ones available. Only six apps were identified as being partially science-based, of which three (50%) were available in at least one app store, and just two of the top 50 recommended apps in app stores (4%) had some scientific basis, but it was not possible to differentiate them from those not based on scientific evidence.

A chat-bot is not a software that needs to be installed in a smartphone or tablet, it respects the privacy of the patient scrupulously, and its learning curve is very short [17]. This computer software has a conversation interface that can both answer questions posed by the user in a natural language (that commonly used by people with all their variants) and ask them questions [18]. Although it is not a new technology, the recent technical revolution for the interpretation of natural languages, together with the above-mentioned advantages and certain downsides of apps, make chat-bots ideal tools for the purposes of this intervention. Since chat-bots “understand” requests expressed with the complexity and variability of human language, they provide a component of technological “humanization” that other interfaces based on menus and chat-buttons lack. This way, they are capable of returning a personalized answer and add a component of user loyalty and usability of the tool [18, 19].

The chat-bot to be evaluated in this trial has been specifically designed by experts in tobacco addiction and artificial intelligence incorporating gamification, cognitive-behavioral, motivational, problem-solving, and relapse-preventing components. Such components form an integral part of science-based interventions recommended by clinical practice guidelines [3, 4].

We aim to assess whether the effectiveness of the usual intervention in primary care can be improved [2] by providing healthcare professionals with guidance to help patients accept the offer to quit smoking [10], so that their motivation to intervene on their patients will increase by decreasing their workload. We also estimate that this type of intervention will improve the accessibility of patients to an evidence-based treatment.

The wide scale and severity of consequences of tobacco use, benefits derived from cessation, low rates of intervention by healthcare professionals, and new opportunities stemming from novel communications technologies in addition to the absence of scientific evidence on its effectiveness and the lack of such tools designed by experts according to the guidelines of the evidence-based clinical practice guidelines are the main factors motivating this project.

## Methods

### Aims

#### Main objective

To assess the effectiveness of an intervention in primary healthcare to help smokers cease their tobacco addiction via a chat-bot for smartphones compared to usual practice, as measured through biochemical validation of continuous abstinence at 6 months.

#### Secondary objectives

To assess the intervention effectiveness compared to usual practice as measured through self-reported continuous abstinence at 6 months.To assess the intervention effectiveness compared to usual practice in terms of the improvement in their quality of life measured by the EuroQol-5D-5 L questionnaire.To evaluate the cost-utility ratio of the intervention compared to usual practice in primary healthcare.To assess the intervention effectiveness in terms of improved adherence to pharmacological treatment for tobacco cessation.

#### Design

The clinical trial will be pragmatic, randomized, controlled, and multicentric. It will last one year, six months for recruiting and six months of follow-up. A cost-utility study will be conducted from the perspective of the funder for a 1-year timeframe. (Figs. 1,2)

**Fig. 1 Fig1:**
[figure not shown]
Protocol

**Fig. 2 Fig2:**
[figure not shown]
Pat plot intervention Dej@lo

#### Setting

Primary healthcare centers in the Madrid Regional Health Service

#### Participants

Patients > 18 years of age who smoke and attend their primary care doctor or nurse consultation during the inclusion period.

### Criteria for inclusion

Healthcare centers: Doctors and nurses from 34 healthcare centers in the Madrid Regional Health Service who agreed to participate, amounting to a total of 248 participants.Patients: Being > 18 years of age; having smoked more than one cigarette per day during the last month; accepting the offered help to quit smoking in the following month; owning a smartphone where a messaging app can be installed; being reachable during the six months following the beginning of the intervention; agreeing to participate and signing informed written consent.

The criteria for exclusion are: Significant communication barriers; Addiction to other substances; And participating in another dishabituation program or clinical trial during the study period.

#### Sample size

The sample size was calculated based on the outcome of a clinical trial recently conducted of usual clinical care in Madrid public health system that employs a similar definition of continuous abstinence as our study [5]. It detected an abstinence rate of 9.6% at 6 months in the control group. We estimate that the intervention to be assessed will double this fig [13, 14]..

Based on these data, and considering a type I error of 5% and a power of 80%, the required number of patients will be 418. After estimating 10% of losses to follow-up, the required sample size is 460 smokers (230 in each group).

#### Recruitment

Each healthcare professional will select patients who smoke, attend the health center for any reason within the recruitment period, and meet the inclusion criteria. They will inform patients about the characteristics of the trial and offer them to participate. Those who accept will be asked to provide informed written consent. In case they decline, their gender, age, and reason for declining will be recorded.

Various strategies will be implemented in order to increase adherence to the protocol by participating researchers, such us personal follow-up upon achievement of protocol objectives and acknowledgement of their effort via e-mail, and offers of certified training sessions.

Randomized allocation: Subjects will be allocated into the intervention or control group by simple randomization using a software installed in the data collection notebook (DCN). This will be done following the inclusion of patients and data collection in the DCN at the initial visit, which guarantees the masking of the randomization sequence to the professionals recruiting patients. The group assigned to the chat-bot will be the intervention group and those treated with usual care by their doctor or nurse will be the control group.

#### Criteria for abandonment and withdrawal

Participants will be able to abandon the study at any time and researchers will be able to withdraw any patient under the following circumstances: not meeting the inclusion criteria; Onset of a severe illness during the clinical trial; Or adverse event, and inability to comply with the study requirements.

The number of abandonments and withdrawals, as well as the reasons for them, will be recorded. Withdrawn patients will not be excluded from the intention-to-treat analysis.

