#### Main effectiveness analysis

Intergroup differences in the continuous abstinence rates at 6 months (main variable) will be analyzed with their CI 95%. Bivariate analysis: a Student’s t-test, or the Mann-Whitney U-test in case the hypothesis of data normality is rejected, will be used to compare the outcome between groups in the case of quantitative variables. For qualitative variables, either Pearson’s chi-squared test or Fisher’s exact test, when applicable, will be used. After adjusting for possible confounding factors, the odds ratio of the association will be calculated using a logistic regression model where the dependent variable will be the continuous abstinence (yes/no) and the independent variables will be patient-related variables and the study group. In all cases, statistical significance will be set at *p* < 0.05. Gained QALYs will be estimated at a population level with their relevant CI 95% via parametric analysis methods and bootstrap techniques. Cost-utility ratio: this aim is exploratory (there is no specific design for it). The cost-utility ratio will be calculated dividing the overall cost by the sum of potential gains expressed in QALYs. For normally distributed data, a multivariate sensitivity analysis will be conducted, making the costs fluctuate within the constructed range of uncertainty. For the same distribution, we will also make the benefits (QALYs) fluctuate within the CI 95%. In all cases, the analysis will be for intention-to-treat. The number of withdrawals, losses to follow-up, and subjects not complying with the protocol will be recorded together with the relevant reasons. Losses to follow-up will be considered as smokers in the analysis [24]. A participant will be considered lost to follow-up after missing two appointments, failing to be contacted by phone in at least two occasions, and having no registered explanation for it. Missing information on professionals and/or patients will be replaced using values from the baseline data.

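### Unmasked staff may withdraw randomised patients on open grounds, and the plan neither keeps their month-6 abstinence measurement nor gives a coding rule that fits them

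*Protocol article*

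**What the plan says.** All references are to the protocol article.

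- **Timing of allocation** (Recruitment): "This will be done following the inclusion of patients and data collection in the DCN at the initial visit". Any withdrawal by staff under the rule below can therefore come after the arm is known.
- **Grounds for withdrawal** (Criteria for abandonment and withdrawal): "researchers will be able to withdraw any patient under the following circumstances: not meeting the inclusion criteria". The list also includes severe illness and ends "Or adverse event, and inability to comply with the study requirements".
- **Criteria that look forward** (Criteria for inclusion): patients qualify by "being reachable during the six months following the beginning of the intervention". A separate exclusion criterion is "participating in another dishabituation program or clinical trial during the study period".
- **Treatment of withdrawn patients** (Criteria for abandonment and withdrawal): "The number of abandonments and withdrawals, as well as the reasons for them, will be recorded", and "Withdrawn patients will not be excluded from the intention-to-treat analysis".
- **Who decides and what they know**: Variables makes the recruiting professionals responsible for follow-up. The Discussion says that the intervention cannot be masked. The blinding described under Masking and in the Discussion is of those who analyse and interpret the data.
- **Coding of missing outcomes** (Main effectiveness analysis): losses to follow-up count as smokers. A loss needs two missed appointments, at least two failed telephone contacts "and having no registered explanation for it". Other missing information is replaced by baseline values.

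**The concern.** Keeping a withdrawn patient in the denominator protects the comparison only if the outcome is still measured. The Masking section relies on an objective outcome to make up for the open design, and that works only where the reading is taken. Here, people who know the arm may end a randomised patient's participation on grounds that leave room for judgement. What counts as a study requirement also differs by arm: downloading a messaging application and using a password on one side, face-to-face visits on the other. If a withdrawn patient is not measured, someone who has quit becomes a failure through a staff decision. If this happens more often in one arm, the difference between arms is biased.

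**Working it through.** **1. How the rules fit together for one withdrawn patient**

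- The patient is randomised, is later withdrawn by staff, and the reason is recorded.
- The patient remains in the intention-to-treat analysis. The article does not say whether the month-6 visit and CO reading still take place.
- If there is no reading, the patient is not a loss as defined, because an explanation is registered. The rule that losses are smokers does not literally apply.
- Under Main outcome variable, abstinence needs the patient's declaration and a CO reading below 10 ppm, so it cannot be confirmed. Under the baseline-value rule the patient takes the baseline state, and every patient smoked at baseline. Both routes give smoker, whatever the true state.

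**2. The plan's own figure**

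Inputs (Sample size): control rate 9.6%, doubled to 19.2%, type I error 5% (two-sided), power 80%. With mean rate p̄ = 0.144:

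n per arm = [1.960 √(2 × 0.144 × 0.856) + 0.842 √(0.096 × 0.904 + 0.192 × 0.808)]² / 0.096² = 208.8, rounded up to 209.

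The total is 418, and 418 × 1.10 = 459.8, rounded up to 460. Both figures reproduce and are not in dispute. Power at 230 per arm with everyone measured is 83.7%.

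**3. Effect of unmeasured withdrawals coded as smokers**

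The article gives no withdrawal rate, so the share w is an assumption, shown for 5% and 10%. I also assume that withdrawal is unrelated to true abstinence. The observed rate is then p × (1 − w), and the understatement is w × p:

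- 0.05 × 9.6 = 0.48 points
- 0.05 × 19.2 = 0.96 points
- 0.10 × 9.6 = 0.96 points
- 0.10 × 19.2 = 1.92 points, and 1.92 / 9.6 = 20% of the target difference

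| Withdrawn, control | Withdrawn, chat-bot | Observed difference (points) | Power at 230 per arm |
|---|---|---|---|
| 0% | 0% | 9.6 | 83.7% |
| 5% | 5% | 9.1 | 81.4% |
| 10% | 10% | 8.6 | 79.0% |
| 0% | 5% | 8.6 | 76.5% |
| 0% | 10% | 7.7 | 67.6% |
| 5% | 10% | 8.2 | 73.6% |
| 5% | 0% | 10.1 | 87.5% |
| 10% | 0% | 10.6 | 90.8% |
| 10% | 5% | 9.6 | 85.7% |

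**4. If the arms truly do not differ**

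With 10% withdrawn in one arm only and observed rates a and b, the rejection rate is Φ((d − 1.96 s₀)/s₁) + Φ((−d − 1.96 s₀)/s₁). Here d = b − a, s₀ is the pooled standard error and s₁ the unpooled one. At a true rate of 9.6%, d = 0.96 points and the type I error is 6.5%. At 19.2%, d = 1.92 points and it is 8.3%.

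**The case against.** The strongest reply is that the article is a condensed text. It keeps withdrawn patients in the analysis, defines a month-6 data visit and records reasons; procedures after withdrawal may stand in the full protocol. Silence alone would indeed be no finding. What remains is that the article itself states the grounds for withdrawal, the definition of loss and the baseline-value rule, and these do not fit together for a patient withdrawn with a reason.

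A reader might also infer more than the documents support:

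- **That outcomes of withdrawn patients are lost.** This is a natural reading of withdrawal from a study, but the article does not say that measurement stops.
- **That both forward-looking criteria are grounds for withdrawal.** The quoted ground names inclusion criteria only. Taking part in another programme is an exclusion criterion and could enter only through a loose reading or as inability to comply.
- **That reachability can be judged only after allocation.** Recruitment has staff select patients who meet the criteria before allocation, so it is first judged as an expectation. Nothing says that it is judged again; the wording merely leaves that open. A patient who stays unreachable has no reading and would be a smoker in any case. The extra harm falls on those unreachable for a time, judged early, or withdrawn for non-compliance.
- **That only controls see a professional.** Recruiting professionals follow patients without distinction by arm, and the Intervention group section refers to medication that they prescribe.
- **That poor chat-bot use is a reason for withdrawal.** The article does not say so, and it lets patients choose the timing and frequency of proactive contacts.

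On size, the objection is right that equal withdrawal of up to 10% costs little: power stays at 79.0% or more against the planned 80%.

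**Conclusion.** The point holds as a weakness that is cheap to remove, not as a demonstrated loss of data. Staff who know the arm may withdraw randomised patients on grounds that leave room for judgement. The text does not secure the month-6 measurement for these patients, and its coding rules would make them smokers without saying so directly. Counting the unmeasured as smokers lowers the rate in each arm, but it is not conservative for the difference when withdrawal is unequal.

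Under an assumed 5% to 10% withdrawn and unmeasured in one arm only, that arm's rate falls by about 0.5 to 1.9 points. The 1.9 is an extreme case: it needs 10% in the chat-bot arm, none in the control arm, none of them measured, and withdrawn patients quitting at the full 19.2%. The direction cannot be known from the article. Withdrawal in the chat-bot arm shrinks the difference, withdrawal in the control arm inflates it, and some combinations cancel. The sample size is not called into question.

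**What to change.** Four changes of wording:

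1. Phrase reachability and non-participation in other programmes or trials as judged at the baseline visit, for example as expected reachability and no current participation.
2. State that later unreachability, joining another programme or not using the chat-bot is recorded with its reason but does not end outcome collection.
3. State that the month-6 visit with CO reading is sought from every randomised patient, including those withdrawn by staff, unless consent is withdrawn.
4. State that every patient without a month-6 reading counts as a smoker, including those withdrawn with a recorded reason, so that the coding does not depend on the definition of loss or on the baseline-value rule.

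These changes concern outcome collection and coding only and leave clinical reasons for stopping the intervention as they are. The article already defines a six-month data visit, so no new visit is needed. The cost is the rewording and a few more follow-up contacts.
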